## Abstract

**Introduction:**

The Chinese herbal compound formula, Shenqisuxin granule (SQSX), promotes neovascularization and prevents in-stent restenosis in modern pharmaceutical studies and is expected to provide an effective strategy for non-ST-segment elevation acute coronary syndrome (NSTEACS). Thus, this study aims to examine the efficacy and safety of SQSX for NSTEACS and initially reveal its mechanism.

**Methods/Design:**

The study is a randomized, double-blinded and placebo-controlled trial. A total of 66 participants will be randomly allocated to one of the following two groups. Participants in the SQSX group will receive conventional treatment plus SQSX, while the placebo group will receive conventional treatment plus placebo, both for 14 days. The primary outcome, hs-CRP, and secondary outcome the Seattle Angina Questionnaire (SAQ) will be assessed at baseline, 7 ± 3 days and 14 ± 3 days. At all visit windows, other indicators including creatine kinase (CK), creatine kinase-myocardial band (CK-MB), cardiac troponins I (cTnI), 12-lead electrocardiograph and the syndrome scores of Qi deficiency and blood stasis will be tested and metagenomic sequencing for intestinal flora will be performed. Echocardiography and safety assessment will be performed at baseline and 14 ± 3 days. Adverse events will be monitored during the trial.

**Discussion:**

The purpose of the study is to examine the efficacy and safety of SQSX to improve NSTEACS and initially reveal its mechanism.

**Trial Registration:**

China Clinical Trial Registry, ChiCTR2000029226. Registered on January 19, 2020.

## Introduction

Non-ST-segment elevation acute coronary syndrome (NSTEACS) is the most common type of acute coronary syndrome (ACS) (1, 2). Despite proven benefits of leading-edge ACS salvage strategies, NSTEACS has a high 1-year main adverse cardiovascular and cerebrovascular events (MACCE) rate of 8.7%, and is associated with a higher risk of long-term mortality (3–5). Thus, it is vital to improve the secondary prevention of NSTEACS and reduce the incidence of MACCE.

High-sensitivity C-reactive protein (hs-CRP) is regarded as an important indicator of the incidence of MACCE. Systemic vascular inflammation plays multiple roles in the presentation of ACS, and hs-CRP is positively associated with the incidence of future MACCE (6–8). The Seattle Angina Questionnaire (SAQ) is widely utilized in the assessment of angina symptoms. The cTnI is an important biomarker to indicate the progression of acute myocardial ischemia. In addition, the disturbed intestinal flora is implicated in forming atherosclerotic plaques (9, 10). The alterations in the intestinal flora are correlated with coronary artery disease (CAD) severity via the mediation of intestinal flora serum metabolites (11). The level of trimethylamine-N-oxide (TMAO) in NSTEACS patients is significantly higher than that in healthy people and is positively correlated with the risk of MACCE (11, 12). Most studies focus on Chinese herbal compounds that act directly on target cells or organs (13). Emerging evidence indicates that Chinese herbal ingredients cannot be absorbed into the blood circulation directly through digestion (14–16). Therefore, the intestinal flora might be an important pathway for Chinese herbs to function.

The Chinese herbal compound formula, Shenqisuxin granule (SQSX) is a novel patented drug (Chinese patent number ZL202010122712.6) for CAD. It comprises six herbs: Huangqi (Astragali Radix), Danggui (Angelicae Sinensis Radix), Danshen (Salviae Miltiorrhizae Radix Et Rhizoma), Ezhu (Curcumae Rhizoma), Huanglian (Coptidis Rhizoma) and Baizhu (Atractylodis Macrocephalae Rhizoma). Based on our previous pharmaceutical studies, the major ingredients of SQSX can activate phosphatidylinositol 3-hydroxykinase-protein kinase B (PI3K-Akt) signaling pathyway and elevate the expression of VEGF mRNA in ischaemic myocardium of rats to promote neovascularization and angiogenesis (17). It can regulate the expression of Ang1/Tie2 and Ang2/Tie2 in hibernating myocardium and promote neovascularization and maturation to improve cardiac function (18). It's also proven that the ingredients of SQSX inhibit the proliferation of vascular smooth muscle cells in the in-stent restenosis minipig model induced by balloon injury, thereby preventing in-stent restenosis (19). At a time when the treatment of NSTEACS has run into a bottleneck, SQSX is expected to provide an effective strategy for further improvement of NSTEACS. Thus, this study aims to examine the efficacy and safety of SQSX for NSTEACS and initially explore its mechanism.

## Methods/Design

### Study Design

The randomized, double-blinded and placebo-controlled trial was endorsed by the Ethics Committee of Xiyuan Hospital, China Academy of Chinese Medical Sciences (Version No. XYYY-ASKY-1.1, January 1, 2021), and registered in the Chinese Clinical Trials Registry (ChiCTR2000029226). Our study conforms to the Helsinki Declaration and the Good Clinical Practice guidelines. It follows the Consolidated Standards of Reporting Trials Extension for Chinese Herbal Medicine Formulas 2017 (CONSORT-CHM Formulas 2017)recommendations and the Standard Protocol Items: Recommendations for Interventional Trials statements (SPIRIT) (20, 21). The study is currently underway at the Xiyuan Hospital, China Academy of Chinese Medical Sciences. Altogether 66 participants will be enrolled and randomly allocated to two groups. All participants will receive their respective interventions for 14 days. The clinical evaluations will be conducted at baseline (Visit 1), days 7 ± 3 (Visit 2) and 14 ± 3 (Visit 3), respectively. Figure 1 depicts a schematic of the study design.

**Figure 1 F1:**
[figure not shown]
Study flowchart.

### Participants

Specially trained research clinicians, the attending physician and general practitioners are responsible for the recruitment. Written informed consent is obtained for entry into the study.

### Inclusion Criteria

Subjects who meet all of the following criteria are eligible to participate in the study: (1) diagnosed as unstable angina (UA) or non-ST segment elevated myocardial infarction (NSTEMI) according to the 2015 ESC guidelines for the management of NSTEACS (22); (2) diagnosed as the TCM syndrome of Qi deficiency and blood stasis according to the Guiding Principles For Clinical Research Of New Chinese Medicines (23); (3) age 40–60 years; (4) heart function is Killip grade I-II for subjects diagnosed as NSTEMI; (5) in-hospital patients; (6) written informed consent is obtained.

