### Intervention

All participants will be randomly allocated to one of the following two groups. Participants in the SQSX group will receive conventional treatment plus SQSX, while the placebo group will receive conventional treatment plus placebo, both for 14 days. The conventional treatment is based on the NSTEACS guideline issued by the European Heart Association in 2015 (22), including but not limited to the following: (1) anti-myocardial ischemic drugs: isosorbide mononitrate 20mg twice daily; (2) platelet inhibition: aspirin 100 mg once daily and ticagrelor 90 mg twice daily; (3) anticoagulation: enoxaparin 1 mg/kg s.c. twice daily; (4) invasive coronary angiography and revascularization according to the practical condition; (5) high-intensity statin therapy: atorvastatin 40 mg po qn. The composition and daily dosage of SQSX equal to Huangqi (Astragali Radix) 50 g, Danggui (Angelicae Sinensis Radix) 10 g, Danshen (Salviae Miltiorrhizae Radix Et Rhizoma) 30 g, Ezhu (Curcumae Rhizoma) 20 g, Huanglian (Coptidis Rhizoma) 10 g and Baizhu (Atractylodis Macrocephalae Rhizoma) 10 g. The placebo is made up of 5% granule and 95% dextrin with a look, smell and taste similar to active granule. Both SQSX and placebo (both 10 g per bag) are produced by Beijing Kangrentang Pharmaceutical Co., Ltd. (Beijing, China) in full accordance with the standards of Chinese Pharmacopeia and Good Manufacturing Practice. They use the same package with the study name and drug number printed on the surface. Subjects will be told to mix the granules with 100 mL of boiled water until dissolved and to drink it 30 min after breakfast and dinner. (10 g at a time, twice a day). To ensure adherence, study medicine will be distributed and/or retrieved at each visit.

During the study period, the use of any other Chinese medicine for the treatment of CAD is forbidden. Antibacterial drugs, probiotic drugs, proton pump inhibitors, immunosuppressants, hormones, drugs for gastrointestinal diseases, and drugs with a direct effect on intestinal flora are not permitted.

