### Sample Size Calculation

The sample size was estimated using hs-CRP. Currently, the hs-CRP of NSTEACS decreased from 5.30 mg/L to 3.74 mg/L after 14 days of conventional treatment, with a decline rate of 29.43% (26). The hypothesis is that the treatment group could reduce the hs-CRP of NSTEACS by 35%. With a type I error rate of α = 0.05 and a power of 80% (a type II error rate of β = 0.2), one arm requires a sample size of 27. With a 20% drop-out rate, we have to recruit a total of 66 patients. The following is the formula for calculating sample size (27):

$$\begin{array}{l} \text{n}=2{\left[\frac{\left({\text{u}}_{\alpha }+{\text{u}}_{\beta }\right)}{\delta /\sigma }\right]}^{2}+\frac{1}{4}u_{\alpha }^{2} \end{array}$$

n, is the sample size required in each group, δ = μ_1_-μ_2_, is the difference between means of two groups, σ, is the standard deviation, u_α_ and u_β_ are the values of u corresponding to the test level α and type II error probability β, respectively.

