### Statistical Analyses

An independent biostatistician will perform statistical analysis. The result of recruitment, the specific reasons for data missing and the distribution of each statistical analysis data set will be described. The primary outcome, the change values of hs-CRP from recruitment to day 7 ± 3, day 14 ± 3 and the day of revascularization, and the secondary outcome, the change scores in five dimensions of SAQ at the same time, are both continuous variables. For comparison between groups, the continuous variables will be described using means ± SD, median, interquartile range, etc., and the Shapiro-Wilk normality test and Levene test for variance homogeneity will be performed. A Student *t* test will be used to compare two groups that have a normal distribution with homogeneous variance, otherwise the Wilcoxon rank-sum test will be used. When some continuous variables are converted into categorical variables, these categorical variables will be described using rates, and the chi-square test or Fisher's exact probability method will be used. For comparison within groups, the paired *t* test or Wilcoxon signed-rank test will be used for continuous variables and the McNemar test for categorical variables. If there are baseline imbalances, Cox regression analysis, logistic regression and multivariate analysis of covariance will be used to adjust confounding variables. The longitudinal data with repeated measures will be analyzed using the linear mixed-effects model to assess associations. The safety analysis will tabulate a detailed description of the adverse reactions, adverse events and serious adverse events and compare the difference in incidence between two groups using Fisher's exact probability method. A difference of *P* < 0.05 at two-tailed test will be considered statistically significant in all analyses. The statistical analyses will be performed using SAS software version 9.4 (SAS Institute, Cary, NC, USA).

After metagenomic sequencing is completed, microbiota community structures will be compared at different taxonomic levels. The abundance and diversity of intestinal flora will be analyzed. The relationship between microbiota composition and clinical outcomes will be investigated using univariate and multivariate linear and nonlinear mixed and regression models. Gene annotation will be conducted to study the function of the intestinal flora.

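### The baseline hs-CRP sample need not precede revascularisation and prior conventional treatment is not limited, so one primary component can be undefined and baselines are not comparable

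*Protocol article*

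**What the plan says.** All references are to the protocol article.

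- **Inclusion Criteria.** The list is presented as complete: "Subjects who meet all of the following criteria are eligible to participate in the study". Patients must be "diagnosed as unstable angina (UA) or non-ST segment elevated myocardial infarction (NSTEMI) according to the 2015 ESC guidelines", and they must be "in-hospital patients". No item gives a time from onset, admission or start of treatment.
- **Exclusion Criteria.** None of the ten items concerns time since the event, length of conventional treatment, or revascularisation before entry.
- **Intervention.** Conventional treatment includes "invasive coronary angiography and revascularization according to the practical condition". The section does not say whether this comes before or after the baseline sample.
- **Table 1.** hs-CRP is first measured at D1 (Visit 1), after a screening visit. No maximum interval from admission is given, and no column covers the day of revascularisation.
- **Statistical Analyses.** The primary outcome is "the change values of hs-CRP from recruitment to day 7 ± 3, day 14 ± 3 and the day of revascularization".
- **Sample Size Calculation.** Planning assumes that "the hs-CRP of NSTEACS decreased from 5.30 mg/L to 3.74 mg/L after 14 days of conventional treatment".

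**The concern.** Two parts of the plan rely on a timing that eligibility does not secure.

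First, a change from recruitment to the day of revascularisation makes sense only if recruitment comes first. The criteria allow the opposite order.

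Second, the day 14 change is planned from a fall seen over 14 days of conventional treatment. Under the criteria, a patient on the first hospital day and a patient already treated for several days are equally eligible. Their D1 samples sit at different points in the course of care, so the same change score need not mean the same thing in both.

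At stake are a primary component that does not exist for some patients, avoidable between-patient variation in a trial of 66, and possibly a smaller effect left to detect.

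**Working it through.** **1. The order of events.**

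| Section | What it fixes about order |
|---|---|
| Inclusion and Exclusion Criteria | Nothing |
| Intervention | Revascularisation as needed, not tied to D1 |
| Table 1 | First hs-CRP at D1, none at screening |
| Statistical Analyses | Assumes revascularisation follows recruitment |

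Take a patient who is revascularised in hospital on the day before D1. No criterion excludes this patient. The schedule holds no hs-CRP value on or before the day of the procedure. If a routine value happened to exist, the change would run backwards in time. The third primary component is therefore undefined for this patient. The day 7 and day 14 changes can be computed, but from a baseline taken after the procedure.

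**2. The planning figures.**

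- Control fall: 5.30 − 3.74 = 1.56 mg/L, and 1.56/5.30 = 29.43%. This reproduces the stated rate.
- Assumed fall on SQSX: 0.35 × 5.30 = 1.855 mg/L.
- Planned arm difference: 1.855 − 1.56 = 0.295 mg/L.
- The stated 27 per arm cannot be checked, because σ is defined but given no value. Solving the article's formula for σ with a two-sided α of 0.05 and 80% power: √[(27 − 1.96²/4)/2] / (1.96 + 0.842) = 1.288. This gives σ ≈ 1.288 × 0.295 = 0.38 mg/L.

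**3. Can the loss be sized?** Not from the article. It gives two points, at the start and end of 14 days, and no shape between or beyond them. The following is a what-if, not an estimate. It assumes the back-solved σ of 0.38 mg/L, and that the arm difference shrinks in proportion to the average share of the 14-day course already run at baseline.

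| Share already run (assumed) | Arm difference, mg/L | Power at 27 per arm | Needed per arm |
|---|---|---|---|
| 0% | 0.295 | 81% | 27 |
| 10% | 0.266 | 73% | 34 |
| 25% | 0.221 | 57% | 48 |
| 50% | 0.148 | 30% | 106 |

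The table shows only that so small a planned difference leaves little room for dilution. It does not show that dilution of any given amount will occur.

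**The case against.** Several counter-arguments carry weight.

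- **A reader might infer a fixed loss per day of delay**, by dividing 1.56 mg/L by 14 days to get about 0.11 mg/L per day. This does not follow. If the fall were linear and continued, the change from entry day t to day t + 14 would be 14 × 0.111 = 1.56 mg/L whatever t is, so the change score would not depend on entry day. A loss requires the fall to slow or stop, and the article says nothing on that.
- **A reader might infer that chance imbalance in entry time could easily mimic the planned effect.** On the same per-day reasoning this takes a mean imbalance of 0.295/0.111 = 2.65 days. With 33 per arm and an assumed entry-time SD of 3 days, the standard error of the difference is 3 × √(2/33) = 0.74 days, so 2.65 days is about 3.6 standard errors. At an assumed SD of 5 days it is still about 2.2. Allocation is randomised and double-blind, and chance imbalance is part of what the 5% test allows for.
- **A reader might infer that late entrants differ from the population behind the 29.43% fall.** That depends on when the cited study took its baseline. The article does not say, and that study may have enrolled ordinary inpatients too.
- **The plan evidently intends revascularisation to follow recruitment**, since the outcome is worded that way. This stands as a reading of intent, but intent in the analysis section is not an entry rule.
- **Hospital stay limits entry time in practice.** This is true, but informal. The criteria go into detail on creatinine, glucose and GRACE score, so a missing timing rule is not obviously just condensed text.
- **A hard window from admission would split the trial**, because 20 patients had completed follow-up. This stands, and is why a window is only optional below.

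**Conclusion.** The point holds in a limited form. Eligibility does not ensure the order of events that the primary outcome presupposes, and anyone revascularised before D1 has no valid value for the component ending on the day of revascularisation. This follows from the text alone and needs no assumption. How many patients are affected is not known.

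Unlimited prior conventional treatment can add variation to the change score and dilute the effect. Its size cannot be computed, since both the hs-CRP course and the SD are missing. Both arms are affected alike in expectation, so the documents do not support a claim of systematic bias. The matter is a moderate weakness in how baseline is defined, worth correcting because correction is cheap.

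**What to change.** 1. **Further recruits.** Add to the criteria that the baseline hs-CRP sample is drawn before any revascularisation for the index event, so that Inclusion Criteria, Intervention and Statistical Analyses agree. This governs who is recruited and when the sample is taken. It does not touch whether or when a patient is revascularised.
2. **All patients, including those already enrolled.** Record the time from admission (or start of conventional treatment) to the baseline sample, and whether revascularisation came first.
3. **Analysis.** Prespecify both as covariates, with baseline hs-CRP, in the hs-CRP model or in a sensitivity analysis: hs-CRP change = arm + baseline hs-CRP + time to baseline sample + prior revascularisation (yes/no). The present text adjusts only if baseline imbalances appear and does not name these variables. No analysis had been run at the time of the article, so this can still be fixed in advance.
4. **Optional.** An entry window from admission. The documents give no basis for a particular length, so that is for the sponsor to choose and justify.

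**Cost.** A protocol amendment, the loss of inpatients already revascularised when identified, and a little extraction of dates that should be in the hospital record. With 20 of 66 patients completed, the new rule can reach at most 66 − 20 = 46. The covariates are what bring the earlier patients into line.

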### Exclusion Criteria

Any of the single conditions as follows would be excluded: (1) indication for renal insufficiency, blood serum creatinine (Scr) > 220μmol/l in males or Scr > 175 μmol/l in females; (2) significant abnormalities in liver function with alanine transaminase (ALT) and aspartate transaminase (AST) are 3 times above the upper bound of normal; (3) systolic pressure > 160 mmHg or diastolic pressure > 100 mmHg after controlled; (4) diabetic patients with random blood glucose ≥ 13.7 mmol/l or glycosylated hemoglobin ≥ 9.5%; (5) Women who are pregnant, breast-feeding or preparing to be pregnant; (6) combined with acute cerebrovascular disease,severe hematopoietic diseases, psychiatric disorder, or malignant tumor; (7) intestinal disease with inflammation or malabsorption; (8) participated in other clinical trials within 3 months; (9) GRACE score > 140 points (high risk group with 1~3% in-hospital death rate) (24); (10) had received antibiotics, steroids, laxatives, antidiarrheals or probiotics within the preceding 3 months.

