**Patients**				
Inclusion/exclusion criteria		×		
Informed consent	×			
General information ^a)^	×			
Medical and treatment history recording	×			
Randomization and allocation	×			

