## Discussion

Based on our previous pharmaceutical studies, SQSX shows a good pharmacological effect of neovascularization and preventing in-stent restenosis. In clinical practice, it's also widely prescribed as a complementary medicine for CAD. Therefore, we would like to initiate a randomized, double-blind, placebo-controlled trial to examine the efficacy and safety of SQSX for NSTEACS. ACS is usually accompanied by gastrointestinal ulcers or bleeding (28, 29), and long-term use of antiplatelet drugs or combined use of multiple anticoagulant drugs causes gastrointestinal mucosal damage (30, 31). These pathological states of the intestinal mucosal barrier cause translocation and disturbance of intestinal flora (32). The disturbed intestinal flora and its metabolite TMAO are one of the reasons that promote the progression of CAD (12, 33, 34). As is well known, NSTEACS is at a critical stage from stable to unstable, which is likely to be accompanied by significant changes in the intestinal flora. We consider that SQSX could be an effective intestinal flora regulator, helping to ease the short-term symptoms of NSTEACS by improving intestinal flora disturbances and gastrointestinal tract injury. The study is possible to provide evidence for the use of intestinal flora modifiers in the treatment of ACS. The above hypotheses are still unclear, so we intend to verify in this trial.

There are three limitations to this work. First, the sample size of the study is small and might be biased. Therefore, two subsequent clinical studies with a larger sample size (*n* = 120) will be launched this year as a follow-up supplement. Second, the biomarker hs-CRP is observed as a surrogate indicator for the incidence of MACCE and does not yet fully explain the efficacy. We'll determine whether or not to investigate the incidence of MACCE further according to the result. Third, we only control the effects of combined medications on the intestinal flora, and could hardly standardize the patient's eating habits and other multivariate factors that affect intestinal flora. We will educate patients and document their dietary and lifestyle habits to ensure consistency of multiple factors as much as possible.

To conclude, the purpose of the trial is to examine the efficacy and safety of SQSX for NSTEACS and explore the possible pharmacological mechanisms.

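### The 3-month look-back in exclusion (10) does not cover SQSX itself, so a recent user of the study drug can enter with an already exposed baseline

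*Protocol article*

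**What the plan says.** Exclusion Criteria is a numbered list of ten items. Item (10) is the only one that looks back at earlier medication by class; it excludes patients who "had received antibiotics, steroids, laxatives, antidiarrheals or probiotics within the preceding 3 months". Item (8) excludes recent participation in another trial, so it catches SQSX only if the patient took it as a trial drug. No item names SQSX or any Chinese medicine.

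The restriction on Chinese medicine is in the Intervention section and is limited in time: "During the study period, the use of any other Chinese medicine for the treatment of CAD is forbidden". The next sentence adds further on-study bans, among them "drugs for gastrointestinal diseases, and drugs with a direct effect on intestinal flora are not permitted".

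The Discussion says that SQSX is "also widely prescribed as a complementary medicine for CAD". It also puts forward the idea that "SQSX could be an effective intestinal flora regulator", and says that this has yet to be verified.

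In Statistical Analyses the primary outcome is "the change values of hs-CRP from recruitment" to later time points. Table 1 places the first hs-CRP measurement and the first stool sample on day 1, and lists "Medical and treatment history recording" at screening.

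**The concern.** Item (10) keeps out recent users of drugs that could disturb the gut or the inflammatory state at baseline. By the investigators' own hypothesis SQSX belongs in that group, and it is the drug under test. The article gives reason to expect some prior users: it reports wide prescribing for coronary disease, and the trial recruits coronary inpatients at a hospital of the China Academy of Chinese Medical Sciences who must also carry a Chinese-medicine syndrome diagnosis.

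For a patient who took SQSX until admission, three things follow:

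- The day-1 hs-CRP is measured after exposure, so the change from recruitment no longer starts from an unexposed value.
- The day-1 stool sample, which is the reference for the mechanism aim, is also taken after exposure.
- If assigned to placebo, the patient shows what happens when SQSX is stopped, not what happens without it. Any persisting effect would narrow the difference between the arms.

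**Working it through.** The point rests on the eligibility text, so the main check is to follow one patient through the criteria. Arithmetic only shows what the size depends on.

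**Can a recent user enter?** Take a patient prescribed SQSX for coronary disease until the day of admission, who otherwise meets the inclusion criteria.

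1. Items (1) to (7) and (9) concern organ function, blood pressure, glucose, pregnancy, comorbidity, intestinal disease and GRACE score. None concerns SQSX.
2. Item (8) applies only to other trials, so routine prescription passes.
3. Item (10) lists five classes. SQSX is not among them.
4. The Intervention bans start with the study period. They stop further use but cannot alter exposure before the day-1 samples.

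The patient is eligible.

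**The plan's assumed effect.** Sample Size Calculation gives a control fall from 5.30 to 3.74 mg/L: 5.30 − 3.74 = 1.56, and 1.56 / 5.30 = 29.43%, as stated. Applying the assumed 35% reduction to the same 5.30 gives 5.30 × 0.35 = 1.855. The assumed difference between arms is 1.855 − 1.56 = 0.295 mg/L.

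**What dilution would depend on.** Let q be the share of recent SQSX users, equal in both arms in expectation, and c the share of the SQSX effect that persists to day 14 after stopping. Suppose a prior user is already fully treated at baseline.

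- Continuing on SQSX, the patient shows the conventional-treatment fall and no further drug effect.
- Switched to placebo, the patient shows that fall less the part of the drug effect that is lost, (1 − c) × 0.295.
- The difference between arms among prior users is therefore (1 − c) × 0.295; among all others it is 0.295.

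Averaging: contrast = 0.295 × (1 − q × c).

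Neither q nor c is in the document. With assumed values:

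| q (assumed) | c = 0 | c = 0.5 | c = 1 |
|---|---|---|---|
| 5% | 0.295 | 0.295 × 0.975 = 0.288 | 0.295 × 0.95 = 0.280 |
| 20% | 0.295 | 0.295 × 0.90 = 0.266 | 0.295 × 0.80 = 0.236 |

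With no persistence the contrast is unchanged whatever q is. The number of exposed baseline samples does not depend on c: 66 × 0.05 = 3.3 to 66 × 0.20 = 13.2, or about 3 to 13 of 66 under the same assumed shares.

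I do not turn this into a statement about power. The article gives no standard deviation, and any such figure would only restate the assumed q and c.

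**The case against.** The case against giving this weight is substantial, and much of it stands.

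**Randomisation.** Prior users are allocated 1:1 like everyone else, so the comparison is unbiased in expectation. A between-arm comparison at days 7 and 14 does not require a drug-naive baseline. This stands. A reader might infer that the trial's result would be biased or invalid; the documents do not support that.

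**Unknown size.** One unquantified sentence supports wide use, while the Introduction calls SQSX novel. Nothing shows that an effect on hs-CRP outlasts treatment, and the flora effect is itself a hypothesis under test. This stands too. A reader might infer a definite loss of power, but that would rest on values of q and c that the article does not contain.

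**History is recorded.** It is, and that allows prior use to be described. It excludes nobody. A reader might go on to fault the plan for adjusting only "If there are baseline imbalances". That does not hold: the covariate list is normally left to the statistical analysis plan, which is not shown, and adjusting for prior use that is balanced between arms would not restore a contrast narrowed by carry-over.

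**On-study bans.** A reader might also infer that the ban is too narrow because it names Chinese medicine only for coronary disease. With gastrointestinal drugs and drugs acting directly on the flora already barred, no harm is shown from what remains, and a wider ban would interrupt treatment for unrelated conditions. The bans do not answer the main point, however, because they start after the exposure that matters.

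**A condensed article.** The article prints a numbered list of ten items, including a drug look-back with its window. The gap is therefore in a criterion as stated, not in a detail left to a fuller document.

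**Conclusion.** The point holds as a modest design improvement. As written, the criteria admit a patient who took prescribed SQSX up to admission, and nothing else in the article protects the day-1 hs-CRP and stool samples from that exposure. The possible consequences are dilution of the hs-CRP contrast, of unknown size and possibly nil, and a less clean baseline for the mechanism aim.

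The conclusion rests on two things: the exclusion list applies as printed, and the Discussion's remark on prescribing means that at least some candidates are recent users. The dilution range additionally assumes q, c and a fully treated baseline in prior users, and serves only as illustration.

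**What to change.** For patients still to be enrolled, add SQSX to exclusion (10) with the 3-month window that the item already uses. The article gives no washout data for SQSX, so the window is chosen for consistency with the item. Keep everyone already randomised in the analysis. Report prior SQSX use by arm from the treatment history taken at screening, for patients enrolled before and after the change.

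The cost is an amendment to one item and slightly slower recruitment. Trial Status reports 20 participants who have completed follow-up and no analysis so far, so at most 66 − 20 = 46 remain to be enrolled. If an assumed 5% to 20% of otherwise eligible candidates are recent SQSX users, filling 46 places needs 46 / 0.95 = 48.4 to 46 / 0.80 = 57.5, or about 49 to 58 candidates. Eligibility will differ slightly before and after the amendment, which reporting by period makes visible.
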